**Figure 5 figure5:**
[figure not shown]
Example of one aspect of the safety planning activity as seen in mindLAMP.

For the purposes of this study, SDM will be defined as the process when provider and client review available treatment options and when clients are encouraged to select the treatment plan that best fits their personal preferences [27]. Previous studies combining app technology and SDM interventions have been mixed [28], and several limitations have been identified, such as time constraints and provider bias toward which patient could benefit and which situation calls for the intervention [29]. However, our team will use this tool for the purposes of discussing and creating short-term therapeutic goals with participants. In addition to clinical conversations, SDM practices will be reinforced through out-of-session activities available through the app. Figure 6 provides an example of one goal-tracking activity as it appears in mindLAMP.

**Figure 6 figure6:**
[figure not shown]
Goal tracking in mindLAMP.

Once each of the clinical visits are over, participants will meet with the digital navigator to review any app-related questions or concerns. The digital navigator will also work with participants and clinicians to ensure that a connection between app data and clinical goals is clear.

### Session Two: Identifying Thought Patterns

The second skill will focus specifically on understanding and identifying thought patterns. CBT will be introduced using a core CBT principle, ensuring information is presented in a structured and educational method, which allows for in-the-moment focus and client participation [30]. Again, mindLAMP will assist in this process by providing clients with out-of-session education and activities. mindLAMP activities will include documenting, describing, and labeling different types of thinking patterns.

Studies have shown that CBT smartphone apps have therapeutic potential [31]; however, like many apps, high user engagement and sufficient long-term outcomes seem to be the top barriers for effective CBT app outcomes [32]. User engagement will be closely monitored through review of out-of-session activities, incorporating participant feedback when applicable, and monitoring participants overall engagement to care. Figure 7 provides an example of a mindLAMP activity that can be used for this skill.

**Figure 7 figure7:**
[figure not shown]
The thought log allows participants to label and track thought patterns in real time.

### Session Three: Identify Coping Skills and Defense Mechanisms 

In session one, a safety plan was cocreated using participant’s language and clinician guidance. In this session, beneficial coping skills will now be identified and discussed in more depth, allowing coping skills to be the main clinical focal point.

To the best of our team’s knowledge, there are no psychodynamic mental health apps that have been widely tested and made available to the public. Providing short-term psychodynamic treatment presents many challenges (time constraints, adequate provider training, bias toward newer clinical modalities); however, recent studies continue to test new ways psychodynamic practices can be beneficial [33]. Therefore, this session will help participants learn and identify some defense mechanisms and help bridge the connection between defense mechanisms and coping skills. The mindLAMP activity will include a list of defense mechanisms (terms, definitions, and examples) and ask participants to link their preferred coping skill with a defense mechanism (if applicable).

### Session Four: Cognitive Defusion

In this session, participants will learn therapeutic skills that offer broad applicability. Specifically, they will learn cognitive defusion, an ACT intervention, which asks participants to notice their thoughts (nonjudgmentally and without identifying with them), acknowledge them, and then let those thoughts leave one’s mind [34].

ACT techniques can be taught in a time-limited fashion, and the straightforward approach can be practiced independently once understood. In a 2-week trial, Levin et al [35] found that participants who used an app intervention to practice ACT skills believed the method was helpful and accessible; furthermore, participants’ depression, anxiety, and psychological flexibility also showed significant improvement. Similar to other clinical skills, cognitive defusion will be practiced through the mindLAMP app by listing the steps of cognitive defusion, asking participants to practice the skill, and then providing space for participants to summarize their experience (see Figure 8 for example). Aspects of session four and the mindLAMP thought log (Figure 7) can be used as well.

**Figure 8 figure8:**
[figure not shown]
Example of mindLAMP’s journal section, which allows participants space to freely reflect on experiences.

### Session Five: Behavioral Activation

Session five will continue to develop participants’ tool kit of therapeutic skills. Modern day behavioral activation techniques include encouraging clients to become aware of avoidance behaviors and places extra emphasis on understanding environmental factors rather than thought patterns [36]. The broad applicability of these skills makes them ideal for TECC and meeting the needs for diverse populations.

Although research on behavioral activation through mobile apps is nascent, one qualitative study found that, when using app interventions, participants felt their treatment was more accessible, were more motivated to engage, and felt security [37]. The behavioral activation mindLAMP activity will include a list of step-by-step instructions and provide space for participants to share their experience.

### Session Six: Mindfulness

Broadly, mindfulness skills ask participants to focus on aspects of their present state as well as factors in their immediate surroundings in a nonjudgmental way. Additionally, practicing mindfulness has been thought to enhance self-awareness, openness to new experiences, and provide users with a deeper understanding of self [38]. Mobile technology studies, including a 2018 randomized trial and a separate efficacy-based investigation, found mobile app interventions could reduce stress and irritability, and yielded statistically significant efficacy measures [39,40]. Mindfulness techniques will be practiced through mindLAMP by providing instructions on how to engage with the technique; participants will again have the option to document their experience (see Figure 9 for example).

**Figure 9 figure9:**
[figure not shown]
Example of one of the guided mindfulness exercises offered in mindLAMP.

### Session Seven: Skills Card

This session introduces participants to a means to reflect on their mental health and build emotional self-awareness. Similar to a DBT diary card (where individuals document and monitor symptoms and behavioral skills used) participants will cocreate a skills card to help practice, identify, and monitor interventions learned and used in their daily lives. App-related DBT studies have shown potential in allowing users to learn and practice a wide range of skills; however, major barriers include app navigation challenges and difficulties understanding interventions without prior DBT exposure or clinical support [41,42]. Nonetheless, increasing symptom awareness and tracking, via diary cards, have been shown to be helpful for various conditions, including those in jeopardy of heart failure, chronic bronchitis, and pulmonary diseases [43,44].

### Session Eight: Patient Activation and Empowering

Based on the Right Question Project, this skill will empower participants to take an engaged role in care by actively asking questions that will encourage clients to participate in the decision-making process [45]. Additionally, the clinical team will pay special attention to ensure culturally appropriate language and values are considered when practicing this skill. Research on apps that support this particular skill is limited. mindLAMP will provide support by encouraging participants to practice advocating for themselves in clinical care by using the skills they have learned throughout treatment and using them outside of clinical sessions.

### End of Study

At the end of the eight-session study, handouts of the data collected and skills learned throughout the study will be given to participants and briefly reviewed a final time. Participants will also be asked to complete a more extensive patient satisfaction survey, which will assess both the clinical sessions and general review of the mindLAMP app. Finally, before ending the study, participants will have a chance to provide verbal feedback to all care team members if they choose. Results and graphs created by participants in mindLAMP will also be made available to participant’s referring provider to assist with continuation of care and build a connection between mental health and additional health care treatment.

### Study Measures

Since TECC was designed to collect a number of clinical surveys throughout treatment, the timeline for survey collection was carefully crafted to decrease oversaturation (see Figure 2 for survey timeline). Specifically, participants will be asked to complete the PHQ-9 (which measures depression rates from minimal depression to severe depression) and the GAD-7 scale (a widely accepted anxiety scale that evaluates scores as either mild, moderate, or severe anxiety) on a daily basis [46,47]. Both the PHQ-9 and GAD-7 scales will be loaded on mindLAMP and become available to participants upon downloading.

Prior to each clinical visit, participants will briefly meet with a research assistant who will provide participants with a secure link (via REDCap) to weekly clinical surveys. This could be done via mindLAMP, but we will use a different platform for the purposes of this study. Those presession surveys include the Sheehan Disability Scale, which measures the effects of poor mental health across three domains: work and school, family, and social life [48]; the Primary Care Posttraumatic Stress Disorder-5, which assess for posttraumatic stress disorder [49]; the Behavior and Symptom Identification Scale-24, a symptom assessment scale [50]; a patient motivation scale, to asses participants commitment to change through treatment; the World Health Organization Five, a well-being assessment scale [51]; and the Working Alliance Inventory–Short Form, a scale to assess the alliance a patient feels toward the clinician that is known to be a predictor of treatment success (this scale will begin after session one) [52].

Additional nonweekly scales include a participant satisfaction scale, which will be given after session four and at the end of treatment, and the System Usability Scale, which is offered during the termination process and is a well-accepted tool to assess satisfaction around use of mindLAMP and TECC [53]. The technology acceptance model, a well-known implementation science framework, will also be used to assess feasibility of technology-infused care [54]. Since the mindLAMP app is able to automatically capture data about when and how it is used, the study will offer a unique data set on longitudinal use patterns and engagement. A provider-specific satisfaction survey will be given to all referring providers at the end of the study to improve the referral process, assess the relevance of clinical data shared, and streamline continuation of care. Other metrics in this study include engagement with the app, as measured by number of log-ins each day, as well as time spent on each element of the app during each log-in. Basic demographics and measures of socioeconomic status will also be collected during the intake process.

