**Results:**

The results of the TECC study will be used to support or adapt this model of care and create training resources to ensure its dissemination. The study results will be posted on ClinicalTrials.gov, with primary outcomes related to changes in mood, anxiety, and stress, and secondary outcomes related to engagement, alliance, and satisfaction.

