Stage 1 “Creating the Clinical Foundation”: This stage will allow participants to learn and practice shared decision-making by cocreating treatment goals, identifying thought patterns, and identifying coping skills and defense mechanisms. The goal of this stage is for participants to develop a broad understanding of their thoughts and behaviors while beginning to identify strengths and need areas. Participants will also be introduced to clinical language and definitions for shared language to be established.Stage 2 “Building Clinical Skills”: Expanding from the skills learned in stage one, this stage will focus on teaching and practicing cognitive defusion and behavioral activation techniques. The goal for this stage is to expose participants to practical therapeutic skills that can be used across many situations and symptom management.Stage 3 “Solidifying Clinical Gains”: This stage introduces participants to mindfulness techniques, a diary card–like model, and patient activation and empowerment skills. The purpose of this stage is to ensure participants grasp all technical skills and clinical language reviewed throughout treatment to make informed autonomous decisions regarding treatment preferences.

This yearlong study will follow a prospective longitudinal cohort design where all participants will receive the same treatment and smartphone interventions. Based on our own Digital Clinic pilot data, we hypothesize participants will report a treatment response rate—defined as 50% symptom reduction—of improvements in anxiety and depression within the 8 weeks of treatment compared to their initial baseline. We also hypothesize that both rates of app engagement out of sessions, as well as therapeutic alliance measured during sessions, will be correlated with clinical improvements and suggest a mechanism of action for TECC. Furthermore the study will test the feasibility of providing technology-enabled mental health care within an outpatient clinical setting via virtual telehealth visits, explore the linguistic and cultural appropriateness of the smartphone app (mindLAMP) used in the study, and analyze the symptom changes of anxiety and depression for all study participants.

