## Methods

### Study

The study will take place at Beth Israel Deaconess Medical Center (BIDMC), a Harvard affiliated teaching hospital in Boston, Massachusetts. The care team will include a psychiatrist, social worker, and digital navigator. The psychiatrist and social worker will provide clinical treatment, education, and support for all participants. The digital navigator, as previously discussed, will be available for technology support and mindLAMP training to other care team members and research participants.

For this study, 50 participants will be enrolled and will not be financially compensated for their participation in TECC. Given the success of the pilot Digital Clinic program, including 50 participants is feasible and necessary to collect a diverse sample and see significant effects of different techniques on clinical assessments of depression and anxiety. This study will be open to any adult (18 years or older) who is interested in using smartphone technology to augment their mental health care. Participants are required to meet the criteria for either mild to moderate depression or anxiety as measured on the Patient Health Questionnaire-9 (PHQ-9) or Generalized Anxiety Disorder-7 (GAD-7) scale. Participants must have daily access to a smartphone, be willing to download the mindLAMP app, use their smartphone for mental health care (both in and outside of session time), and be open to learning about an array of clinical modalities (dialectical behavior therapy [DBT], cognitive behavioral therapy [CBT], short psychodynamic therapies). For participants who do not own a smartphone, the care team will help individuals sign up for a free phone through the US Federal Government’s Project Lifeline if they are eligible. Participants must also be affiliated with a BIDMC or Beth Israel Lahey Health provider and be available for eight clinical sessions (telehealth) over the course of 2-4 months. Until the Spanish language version of the mindLAMP app has been properly vetted, participants must be able to read, write, and communicate in English at an eighth grade level. Recruitment efforts for TECC include digital flyers and brief informational sessions for referring providers.

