### Interventions

Interventions for TECC will be employed through a multipronged approach including in-session care from clinicians, exposure and education to evidence-based therapies, use of the mindLAMP app, and technology support from the digital navigator.

At least 1 week before the initial clinical visit, participants will meet with the digital navigator to download the mindLAMP app, receive app training, and will be asked to begin completing the mood surveys (PHQ-9 and GAD-7) in mindLAMP on a daily basis. During the meeting, participants will be informed the app will not be used to offer emergency services between sessions and app responses will not be monitored outside of clinical sessions. A signed waiver will be presented to reflect this understanding.

The format for TECC sessions will follow the pre-established Digital Clinic structure (Figure 1). Specifically, before each clinical session, participants will be required to complete a variety of clinical surveys. These surveys will be made available through the clinic’s secured, research-based survey platform (REDCap, Vanderbilt University). The surveys (see Figure 2 for more details) are designed to help clinicians develop a comprehensive understanding of each participants progress throughout the study. Once the clinical portion of the session starts, any mindLAMP data collected will be reviewed and discussed. This step will ensure the data in mindLAMP accurately reflects the participant’s lived experience and ensure the personalized nature of each patient’s care is reflected in the session. Next, the clinician will discuss a predetermined clinical skill, and the clinician will work to relate the skill to the patient’s unique needs. The clinician will introduce the skill by describing its purpose, giving examples of when the skill can be used, and explain how the skill could impact the participants mental health needs. With clinician guidance, participants will then practice the skill, brainstorm scenarios in which the skill could be used, and review a skill-building activity (see Multimedia Appendix 1 for details). Activities will be conducted through skill-building modules (eg, mindfulness), informational worksheets, surveys, and free-writing opportunities that will be available through the app. Participants will be encouraged to complete the activities between sessions to strengthen their understanding and comfortability of use with each skill.

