### Further Study Details

All participants will complete a written informed consent for this voluntary study. Participants will be able to withdraw from TECC anytime, just as they can withdraw from routine care at any time. Participants who miss four consecutive sessions will be asked to restart the protocol. During the study, if a participant’s clinical presentation significantly worsens, the clinical team will re-evaluate the participant’s involvement in the study. Intent-to-treat analysis will be applied so that data from all participants, even those who drop out, will be included in the outcomes.

The mindLAMP app meets federal privacy and security requirements, and has been institutional review board (IRB)–approved for use in clinical research. All data collected by mindLAMP will be securely transmitted directly to a server within the hospital network. Additionally, after receiving IRB approval, the TECC protocol will be registered with ClinicalTrials.gov.

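### The only follow-up route described for PHQ-9 and GAD-7 is daily entry in the study app, so missing end-of-treatment scores are tied to app engagement

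*Protocol article*

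**What the plan says.** **Hypothesis and outcomes.** The Introduction expects a treatment response, "defined as 50% symptom reduction", in anxiety and depression within the 8 weeks. It also expects app engagement outside sessions to correlate with clinical improvement and to point to a mechanism. The Abstract announces results "with primary outcomes related to changes in mood, anxiety, and stress", with engagement among the secondary outcomes.

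**How PHQ-9 and GAD-7 are collected.** Under Interventions, participants meet the digital navigator at least a week before the first visit and "will be asked to begin completing the mood surveys (PHQ-9 and GAD-7) in mindLAMP on a daily basis". Study Measures repeats the daily schedule and adds: "Both the PHQ-9 and GAD-7 scales will be loaded on mindLAMP and become available to participants upon downloading".

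**How the other scales are collected.** Before each visit a research assistant gives participants a REDCap link. Of this the article says: "This could be done via mindLAMP, but we will use a different platform for the purposes of this study". The scales then named are the Sheehan Disability Scale, PC-PTSD-5, BASIS-24, a motivation scale, WHO-5 and WAI-SF. End of Study and the list of non-weekly scales mention no closing PHQ-9 or GAD-7.

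**Missing data.** Further Study Details promises an intent-to-treat analysis in which "data from all participants, even those who drop out, will be included in the outcomes". Analysis adds tests for dropout effects. If these are significant, a logistic dropout model and inverse probability weighting follow.

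**The concern.** A PHQ-9 or GAD-7 entry in mindLAMP is itself app use. On the route described, a late score exists only for someone still using the app. Engagement is meanwhile measured in its own right, by log-ins and time spent on each element, and is expected to go with improvement. If that expectation is right, participants without an end score are, on the protocol's own reasoning, likely to be those who improved less.

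Two results are at stake. The change and the response rate at the end of treatment would come mainly from engaged participants and could look better than they would for all 50. The association between engagement and improvement would be estimated with the low-engagement end thinned out.

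**Working it through.** The article states no figure for this point to reproduce. It gives a sample size ("50 participants will be enrolled") but no dropout rate, expected response rate or share expected to stop using the app. The check therefore reads the described routes side by side and then illustrates the possible size on assumed inputs.

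**Step 1. Routes described**

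| Measure | Route in the text | Depends on app use? |
|---|---|---|
| PHQ-9, GAD-7 at eligibility | Not stated | Unknown |
| PHQ-9, GAD-7 during follow-up | Daily in mindLAMP | Yes |
| Sheehan, PC-PTSD-5, BASIS-24, motivation, WHO-5, WAI-SF | REDCap before visits | No |
| PHQ-9, GAD-7 at a fixed end point | None described | – |

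**Step 2. Size of the bias in the response rate**

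Assumed: response 60% among those still entering scores, 30% among those who stopped, share *d* stopped, and an unweighted analysis of the observed scores.

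Full-cohort response = (1 − *d*) × 60% + *d* × 30%. Overstatement = *d* × (60% − 30%).

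- *d* = 20%: 0.8 × 60 + 0.2 × 30 = 54%; observed 60%; overstated by 6 points.
- *d* = 40%: 0.6 × 60 + 0.4 × 30 = 48%; observed 60%; overstated by 12 points.

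With other assumed rates (50% and 20%) the gap is again 30 points. The overstatement is then 3 points at 10% stopping and 15 points at 50%.

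**Step 3. Bounds with no assumption about those who stopped**

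If 50% of the observed participants respond, the full-cohort rate lies between (1 − *d*) × 50% and that value plus *d*. For *d* = 20% this is 40% to 60%; for *d* = 40% it is 30% to 70%.

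**Step 4. Precision**

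The within-person change detectable with 80% power at two-sided 5% (both assumed) is (1.96 + 0.84)/√n SD. This is 0.40 SD at n = 50 and 0.51 SD at n = 30 (40% stopped). Precision is lost, but bias is the larger problem.

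**Step 5. Can the planned weighting be relied on?**

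It starts only after a significant dropout test. Comparing a continuous covariate between those who stopped and those who continued, at the same assumed power and level, the detectable difference is 2.80 × √(1/n₁ + 1/n₂) SD:

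- 10 stopped, 40 continued: 2.80 × √(0.100 + 0.025) = 0.99 SD.
- 20 stopped, 30 continued: 2.80 × √(0.050 + 0.033) = 0.81 SD.

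Smaller differences, which can still bias the result, would often not trigger the weighting. Once triggered, it uses variables measured at the start of the stage, so it does not capture a change in symptoms after that point. It is also framed around dropout. Someone who attends sessions but no longer enters scores may not count as having dropped out.

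**The case against.** **The route may not be exclusive.** The REDCap list is introduced as what the surveys include, so it need not be complete. Figure 2, whose legend names both scales, is not shown. The platform of the eligibility score is not stated. This stands: the finding can only be that no other follow-up route is described.

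**The plan deals with dropout.** The weighting targets loss related to engagement. It may reduce the bias in Step 2, which assumes no weighting. Its limits in Step 5 remain.

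**Few may attend yet stop entering scores.** The app is used in sessions, its data are reviewed there, and the digital navigator meets participants after each visit. This makes the pattern less likely but does not rule it out, and it does not help with people who leave. Daily scores entered before app use stops are kept; only later ones are lost.

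**An article leaves endpoint windows to the full protocol.** That is fair for the exact window. The collection route, however, is set out in the article itself.

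**Stronger readings that the article does not support.** A reader might infer that no symptom measure exists outside the app. BASIS-24 and WHO-5 are collected through REDCap, and the Abstract names no instrument for the primary outcomes. A reader might also infer from "any mindLAMP data collected will be reviewed and discussed" that the therapy shapes the scores. Joint review of self-reported scores makes this possible, but nothing in the article shows it. REDCap would not remove the possibility either: Interventions says those surveys also serve to inform clinicians, and Results plans in-session review of clinical metrics.

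**Conclusion.** The point holds in a limited form. The article describes no follow-up PHQ-9 or GAD-7 that is independent of app use, so missing late scores are tied to engagement. The intent-to-treat statement cannot supply them, and at N = 50 a weighting step triggered by a significance test may correct the gap only in part.

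The size is unknown. The illustration of 6 to 12 points rests on assumed response rates of 60% and 30%, an assumed 20% to 40% stopping, and an unweighted analysis. With less stopping, a smaller gap between the groups or effective weighting, it would be smaller. If Figure 2 or the full protocol already places both scales in REDCap at the end of treatment for all participants, the concern is largely met and the text need only say so.

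**What to change.** - Add PHQ-9 and GAD-7 to the REDCap set at two points: before session one and at a fixed end-of-treatment point.
- Send the link to every participant, whether or not they still use the app or attend sessions, unless consent is withdrawn.
- Name this pair of readings as the endpoint for change and for the 50% response.
- Keep the daily in-app scores for clinical review and for describing the course over time.
- Keep the planned weighting for whatever remains missing.

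The cost is two completions of 9 + 7 = 16 items per participant, at most 2 × 50 = 100 in all, on a platform already in use. The downside is a little more questionnaire burden in a schedule designed to limit it. Some participants who leave will still not answer, so the change reduces the missing data but does not remove it.

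### The weekly REDCap scales are collected only through a pre-visit meeting, with no stated route after missed sessions or after stopping, so intent-to-treat for these scales rests on scores from while the person attended

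*Protocol article*

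**What the plan says.** Three parts of the Methods bear on this.

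- **Collection route.** Interventions says that "before each clinical session, participants will be required to complete a variety of clinical surveys". Study Measures describes the mechanism: "Prior to each clinical visit, participants will briefly meet with a research assistant who will provide participants with a secure link (via REDCap"). It adds, of collecting these surveys in the app: "This could be done via mindLAMP, but we will use a different platform for the purposes of this study".
- **What travels by that route.** "Those presession surveys include the Sheehan Disability Scale, which measures the effects of poor mental health across three domains"; the list goes on with PC-PTSD-5, "the Behavior and Symptom Identification Scale-24, a symptom assessment scale", a motivation scale, "the World Health Organization Five, a well-being assessment scale", and the Working Alliance Inventory, which begins after session one. PHQ-9 and GAD-7 are handled differently: they are loaded in the app and completed daily.
- **Leaving, and the analysis.** Further Study Details says: "Participants will be able to withdraw from TECC anytime, just as they can withdraw from routine care at any time". It asks those who miss four sessions in a row to restart, and then says: "Intent-to-treat analysis will be applied so that data from all participants, even those who drop out, will be included in the outcomes". The Analysis section adds tests for dropout effects and, if these are significant, a logistic dropout model with inverse probability weighting.

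**The concern.** The planned analysis covers everyone, but the described collection of the weekly scales follows the sessions. A participant who stops attending has no described occasion on which to receive the link, so function, well-being and the session-tied symptom scales would simply end.

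That missingness is unlikely to be neutral. Attendance is part of adherence to TECC, and the Analysis section sets out to relate symptom change to engagement and adherence. The protocol also has the clinical team re-evaluate the involvement of anyone whose presentation significantly worsens; a person who left by that path would give no later score on these scales. Others may stop because they feel better. In either case, change on these scales would describe the weeks people attended, and the direction of any bias would be unknown. Scores after stopping cannot be recovered once the time has passed.

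**Working it through.** The plan gives no dropout rate and no figure for missing surveys, so there is none to reproduce. The check sets the statements side by side and then counts.

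**Which scales are exposed**

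| Scale | Stated route | Tied to a session? |
|---|---|---|
| Sheehan, BASIS-24, WHO-5, PC-PTSD-5, motivation | REDCap link at the meeting before each visit | Yes |
| Working Alliance Inventory | Same, beginning after session one | Yes, and by its nature it needs a session |
| PHQ-9, GAD-7 | Daily in the app, available once downloaded | No |

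The hypothesis at the end of the Introduction (a 50% reduction in anxiety and depression within 8 weeks) concerns what PHQ-9 and GAD-7 measure, so the exposure is confined to the first two rows.

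**Scheduled occasions.** With 50 participants and 8 sessions (Methods, Study), 50 × 8 = 400 presession survey sets are planned.

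**Loss from missed sessions.** The restart rule applies at four consecutive misses.

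- One run of three misses does not trigger it and loses 3/8 = 37.5% of that person's sets.
- The worst case without triggering it: with *k* sessions attended, the 8 − *k* misses fall into at most *k* + 1 runs of at most 3 each. So 8 − *k* ≤ 3(*k* + 1), which gives *k* ≥ 1.25, that is *k* = 2. Attending only sessions 1 and 5 is an example, and yields 2 of 8 sets.

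**Loss from stopping.** A participant who stops after session 3 gives at most 3 of 8 sets and nothing at the end of treatment. The number without an end-of-treatment score is 50 × the proportion stopping early, which has to be assumed:

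| Assumed proportion stopping early | Without end score | With end score |
|---|---|---|
| 10% | 5 | 45 |
| 20% | 10 | 40 |
| 30% | 15 | 35 |
| 50% | 25 | 25 |

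**What the weighting can do.** Inverse probability weighting gives more weight to observed participants who resemble those lost. It can give a valid group estimate if dropout depends only on variables that were measured and are in the dropout model. The daily PHQ-9 and GAD-7 would be useful there. It does not supply scores after stopping, and the data cannot verify that condition. It is also used only if the dropout tests are significant, and with 50 participants those tests may miss a dropout effect that matters.

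**The case against.** The strongest reply is that the main outcomes lie outside this mechanism. That is correct and limits the point to the weekly REDCap scales. No hypothesis in the Introduction names the Sheehan, WHO-5, BASIS-24 or PC-PTSD-5. The abstract and the Analysis section do mention stress as an outcome, and a reader might infer that it is scored from this set; the article assigns no scale to stress, so that cannot be claimed.

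Second, the article does not say in words that the link is withheld when a visit is missed. The meeting comes before the visit, and the survey timeline (Figure 2) could not be read here. This stands as a caution. Still, the only route described runs through that meeting, and the route that does not need a visit is mentioned and set aside.

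Third, an article condenses, and follow-up of people who stop treatment may be set out in the full protocol. That would excuse silence. Here, though, a collection rule is stated, and it fits poorly with the stated analysis aim. It is not a direct contradiction: the intent-to-treat sentence says that dropouts' data will be included, not that every scale continues after dropout.

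Fourth, sessions may be spread over 2-4 months, so a missed one can perhaps be rebooked. This makes the 2-of-8 count a worst case, not an expectation.

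Finally, the weekly surveys are meant to inform the clinician at each session, so moving all of them to fixed calendar dates would fit badly with that window. This stands, and the fix below keeps the presession surveys.

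**Conclusion.** The point holds for the weekly REDCap scales. As described, they are collected around sessions, no route is stated after missed sessions or after stopping, and an intent-to-treat result for them would depend on scores from attended weeks and on conditional weighting with an untestable assumption. It is worth correcting before enrolment because the lost data cannot be recovered.

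The size is illustrative. The 10 to 15 of 50 without end-of-treatment scores follows from an assumed 20% to 30% stopping early, and the article gives no rate.

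Three stronger readings are not supported:

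- *That PHQ-9 and GAD-7 are lost as well.* They do not depend on sessions, and nothing says that stopping sessions ends app data. The article only fails to say that completion continues to be invited.
- *That stopping sessions and withdrawing are treated as one act.* Further Study Details deals with missed sessions separately from withdrawal. What it leaves open is the status of someone who stops sessions without withdrawing.
- *That the analysis amounts to carrying the last score forward.* No such rule appears, and weighting is planned.

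**What to change.** In Study Measures:

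- Keep the presession surveys for attended sessions.
- Send the same REDCap link electronically when a scheduled session is missed.
- Send one end-of-treatment set at a pre-set time counted from session one, within the stated 2-4 month window, to everyone who has not withdrawn consent for data.
- Tie the Working Alliance Inventory to attended sessions only.

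In Further Study Details:

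- State that stopping sessions is not withdrawal from data collection.
- State that daily PHQ-9 and GAD-7 completion in the app continues to be invited after stopping.
- State that scores obtained after stopping enter the intent-to-treat analysis.

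The cost is protocol and consent wording and automated messages from a platform already in use, with no extra visits. The downside is some survey burden on people who have stopped, and their response will be incomplete. The weighting in the Analysis section therefore remains useful, with less left for it to correct.
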